#### 2.6.5. Body Composition Analysis

The body composition measurements will be performed at Visits 2, 5, and 7 using bioelectrical impedance technology with the Tanita Scale DC 430U (Tokyo, Japan). Fat mass percentage, visceral fat rating, and greater muscle mass percentage will be evaluated. Changes in fat mass percentage between Visits 2, 5, and 7 will be considered as the secondary outcome measures. It is expected that in the follow-up larger randomized controlled trial, a more accurate dual-energy X-ray absorptiometry (DXA) method will be used, which was not possible in this pilot trial.

#### 2.6.6. Cardiac Parameters

Systolic and diastolic BP and HR measurements will be done at Visits 2, 5, and 7 under resting (after a 5-min rest) and fasting conditions and will result in an output that was an average of three readings 1–2 min apart. Changes in systolic BP, diastolic BP, and HR between Visits 2, 5, and 7 will be considered as the secondary outcome measures.

#### 2.6.7. Questionnaires

General health questionnaires and chrono-nutrition questionnaires will be collected at Visits 2, 5, and 7. The required permissions from the developers of the questionnaires for the use of non-commercial research purposes were obtained.

The ESS will be used to assess self-reported sleepiness. The BDI-II will be used for measuring depression severity. Sleep quality will be analyzed through the Pittsburgh Sleep Quality Index (PSQI). The Munich Chronotype Questionnaire (MCTQ) will be used to determine the self-reported chronotype. The self-reported health survey (SF-36 health survey) will be used to evaluate self-reported overall health and wellbeing. Regarding the eating disorder examination, the physician at Visit 1 and study investigator at Visits 2 and 3 will examine and interview the patients to determine whether any symptoms of an eating disorder occur. If the symptoms are detected the patient will not participate.

The chrono-nutrition questionnaire will be used to evaluate the habitual timing of dietary intake (frequency, (ir)regularity, and time window) during weekdays and weekends. Participants will be asked to fill in specific clock time points (30-min range) of getting up, eating and drinking (breakfast, lunch, dinner and in-between-snacks). Frequency of caloric intake will be calculated by summing up the number of eating and drinking clock time points. The time window of food and drink consumption will be determined by calculating the difference between the first and last episode when participants ate or drank something. Face validity was assessed and showed that completing the questionnaire takes approximately 10 min, and participants perceived the questionnaire easy to complete.

### 2.7. Primary and Secondary Outcome Measures

The primary and secondary outcome measures are depicted in Table 2. The adherence to TRE intervention is the primary outcome defined as the proportion of the total number of days recorded with mCC app during the TRE monitored intervention period (i.e., between Visit 3 and Visit 5) in which participants satisfied a requirement of a 10-h TRE eating window. The secondary outcome measures include changes in body weight, BMI, waist circumference, fat mass percentage, mean daily glucose levels obtained by CGM, mean fasting glucose levels obtained by CGM, FPG, lipids and HbA1c levels, HOMA-IR, as well as metabolic, neuroendocrine, inflammatory and oxidative stress biomarkers levels, eating window duration and timing of eating collected via mCC app and chrono-nutrition questionnaire, calorie intake collected via mCC app, physical activity and sleep duration collected via mCC app, systolic and diastolic BP, HR, and the health questionnaires scores. The main secondary outcome measures include changes in body weight and FPG between Visit 2 and Visit 5. The time frames for changes in all outcomes are indicated below in Table 2.

### 2.8. Data Collection and Management

Data will be collected by TREMNIOS trial team members with training and experience in clinical assessment. All data related to this study will be stored with the highest possible level of security. Completed data forms or other hard-copy documents containing protected health information will be kept in a locked file in the coordinator’s office at the Department of Medical Biology and Biochemistry, CM. Data will be entered into an electronic deidentified database (for subsequent transfer into SPSS for reporting and statistical analysis) by authorized team members trained in data management; participants will be identified only using a unique number. Electronic data will be stored on a secure server which is maintained, with regular back-ups, by CM system administrators and accessible from password-protected computers in the Department of Medical Biology and Biochemistry, CM. The principal investigator ([name]) and designated team members will review all data collection forms on an ongoing basis for data completeness and accuracy as well as protocol compliance. Access to data with identifiers will be restricted to authorized team members and regulatory authorities. Any data, forms, and other records with identifiers that leave the site will be transported in a locked file box to maintain confidentiality. Identifiable data will be destroyed 5 years after study completion or 3 years after the last publication based on when the data is published, whichever comes last (unless future regulations dictate that the data be kept longer).

### 2.9. Statistical Analysis

Data will be analyzed using SPSS Statistics software (IBM Inc., Armonk, NY, USA). The normality of distribution will be examined for all variables and those found to have a non-normal distribution will be properly transformed before further analysis. Paired samples t-tests will be used to compare baseline to post-intervention value. The adherence to TRE intervention expressed as the percentage of days with achievement of required 10-h eating window during the TRE monitored intervention will be calculated per participant, and then reported as a group mean with standard deviation. A two-tailed *p* < 0.05 will be considered statistically significant.

A sample size calculation was performed which indicated that the TREMNIOS trial has a sufficient statistical power to detect clinically relevant changes in the two main exploratory outcomes, i.e., body weight and FPG. Specifically, using the GPower software (v.3.1.9.7) [62], we calculated that a sample size of 26 (which is consistent with ~10% dropout rate) provides 80% power at the 0.05 significance level to detect an effect size of 0.8 for the main exploratory outcomes of TREMNIOS trial. We note that this effect size is smaller than the previously observed TRE-induced body weight change [34,38,44] and fasting plasma glucose change [35,39,41,50].

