### 2.2. Subjects and Eligibility

A total of 30 participants with MetS and prolonged daily eating duration will be enrolled in the study. The inclusion and exclusion criteria are described in Table 1.

Participants must have FPG of ≥100 mg/dL and two additional indicators of MetS, self-reported dietary intake of ≥14 h per day, regular daytime schedule of activity, self-reported habitual sleep duration of >6.5 h, and a smartphone with Apple operating system (OS) or Android OS [4]. We chose to use FPG as one of the necessary inclusion criteria of MetS diagnosis for several reasons. It is known that high FPG and T2D are common and associated with an increased risk of CVD and mortality [4,56]. High FPG is a prevalent component of MetS-component clusters which are frequent and have an increased cardiovascular risk [1,57,58,59]. Circadian rhythm disruption is associated with abnormal glucose metabolism and it was shown that TRE can improve glucose regulation and maintain blood glucose level within homeostatic range [10,11,12,13,30].

The exclusion criteria include diagnosis of diabetes mellitus, shift work, planned travel over time zones, recent history of major adverse cardiac events, other active or uncontrolled medical conditions, history of eating disorder or bariatric surgery, participation in the weight-management program, special or prescribed diet for other reasons, substance abuse, depression, sleep apnea, and treatment with antidepressants, medication affecting glucose metabolism or appetite, or immunosuppression.

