### 2.6. Measurements

#### 2.6.1. Anthropometry

The anthropometric measurements will be performed at Visits 2, 5, and 7. Participants will have their weight and height measured in the fasted state on a digital scale with a height rod. The accuracy of the measurements is 0.1 kg and 0.5 cm, respectively. Body mass index (BMI) will be calculated using the formula [weight(kg)/height^2^(m^2^)] and the cut-off points of the World Health Organization will be used. Waist circumference will be measured in a fasted state immediately above the iliac crest using an anthropometric tape accurate to 0.5 cm. Changes in body weight, BMI, and waist circumference between Visits 2, 5, and 7 will be considered as the secondary outcome measures. Change in body weight between Visits 2 and 5 will be considered as the main secondary outcome measure.

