The TREMNIOS trial will examine one group of 30 patients (pre-post TRE intervention) with no control group which is a potential limitation. This approach has been chosen given that this trial is a precursor for large-scale controlled trial in the future and available funding at this initial stage of study is limited which limits the overall number of patients. Following the results of power analysis, it is deemed advantageous to conduct a single arm trial with 30 participants rather than the controlled trial with a smaller sample size of each group. Whereas the evaluation of the adherence to the TRE intervention does not require a control group, the interpretation of exploratory data on cardiometabolic parameters will require caution. For example, because there is no control group, one cannot exclude the possibility that TRE-related changes in cardiometabolic parameters will be to some extent affected by the process of monitoring during the TRE intervention. The planned randomized controlled trial to be conducted after the TREMNIOS trial is expected to be free of this limitation. However, the lack of a control group in the TREMNIOS trial may limit the ability to predict the acceptability of participants to be randomized to intervention and control groups in a planned large-scale randomized-control trial.

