**Secondary Outcome Measures**
Body weight ^2,3,4^ Fasting plasma glucose ^2,3,4^ Body mass index ^2,3,4^ Waist circumference ^2,3,4^ Fat mass ^2,3,4^ Mean glucose level as measured by continuous glucose monitor ^2,3,4^ Mean fasting glucose level as measured by continuous glucose monitor ^2,3,4^ Lipids ^2,3,4^ Glycated hemoglobin ^2,3,4^ Homeostasis model assessment-insulin resistance score (HOMA-IR)^2,3,4^ Metabolic and neuroendocrine biomarkers ^2,3,4^ Inflammatory biomarkers ^2,3,4^ Oxidative stress/antioxidant defense biomarkers ^2,3,4^ Systolic and diastolic blood pressure ^2,3,4^ Heart rate ^2,3,4^ Calorie intake collected via the myCircadianClock app ^1,3,5^ Timing of dietary intake collected via the myCircadianClock app and chrono-nutrition questionnaire ^1,2,3,4,5^ Eating window duration collected via the myCircadianClock app and chrono-nutrition questionnaire ^1,2,3,4,5^ Physical activity duration collected via the myCircadianClock app ^1,3,5^ Sleep duration collected via the myCircadianClock app ^1,3,5^ Self-reported sleepiness as assessed from the Epworth Sleepiness Scale ^2,3,4^ Self-reported depression determined by the Beck Depression Inventory-II ^2,3,4^ Self-reported sleep quality as assessed from the questionnaire Pittsburgh Sleep Quality Index ^2,3,4^ Self-reported chronotype as assessed from the Munich Chronotype Questionnaire ^2,3,4^ Self-reported overall health and wellbeing as assessed from the self-reported health questionnaire (SF-36 health survey) ^2,3,4^

Each listed secondary outcome measure should be understood as a change in the measure over time-restricted eating (TRE) intervention period. Time frames for changes: ^1^ between Visits 3 and 5; ^2^ between Visits 2 and 5; ^3^ between Visits 5 and 7; ^4^ between Visits 2 and 7; ^5^ between Visits 3 and 7 (see Figure 1 for details).

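### The 24-week change is to be tested by paired t-test, which ignores the Visit 5 value of anyone lost before Visit 7; a three-visit mixed model would use it at little cost

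*Protocol article*

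**What the plan says.** Section 2.9 of the protocol article gives the analysis of change in one sentence: "Paired samples t-tests will be used to compare baseline to post-intervention value". The criterion is "A two-tailed *p* < 0.05 will be considered statistically significant". No other method for change appears in the article.

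Section 2.6.1 is typical of the schedule: "Changes in body weight, BMI, and waist circumference between Visits 2, 5, and 7 will be considered as the secondary outcome measures". The Table 2 footnotes give most secondary outcomes three time frames: Visits 2 to 5, "between Visits 5 and 7", and Visits 2 to 7. Calorie intake, physical activity and sleep duration from the app use Visits 3-5, 5-7 and 3-7 instead. Timing of intake and eating window carry all five footnotes. Section 2.7 makes the Visit 2-5 changes in body weight and fasting plasma glucose the main secondary outcomes.

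On numbers, section 2.2 states: "A total of 30 participants with MetS and prolonged daily eating duration will be enrolled in the study". Section 2.9 bases power on "a sample size of 26 (which is consistent with ~10% dropout rate"). On design, the Discussion states: "The TREMNIOS trial will examine one group of 30 patients (pre-post TRE intervention) with no control group which is a potential limitation".

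**The concern.** A paired t-test needs both values. Someone measured at Visits 2 and 5 but not at Visit 7 contributes nothing to the 24-week result, although their Visit 5 value carries information about the missing one. The time frames in Table 2 can then rest on different people, so the Visit 2-5 and 5-7 mean changes need not add up to the Visit 2-7 change.

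In a single-arm trial the completer mean is itself the estimate, and no comparison group shares the same selection. Section 2.5 says that investigator feedback and push notifications stop after Visit 5, so any later loss falls in the unsupported phase. The Discussion presents 24-week adherence data as a contribution of this trial. It also says that the results will inform the sample size and intervention length of the planned randomized trial. An inflated 24-week change would carry over into that design.

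**Working it through.** **1. The plan's own figures.**
- 26 of 30 means 4 lost: 4/30 = 13.3%. The stated loss of about 10% would leave 30 × 0.9 = 27, and 26/0.9 = 28.9, so 29 enrolled. Within rounding, 26 and 30 are compatible. They fit an analysis of people with follow-up only, but that is an inference.
- The plan says that 26 "provides 80% power at the 0.05 significance level to detect an effect size of 0.8 for the main exploratory outcomes". For a two-sided paired t-test with a standardised change of 0.8, exact noncentral-t power gives 15 pairs for 80%, and 26 pairs give 97.5%. The figure 26 is reproduced only as the per-group size of a two-independent-sample test (80.7% power). That is a separate matter; here 26 serves only as the number analysed.

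**2. Size of the bias in the completer mean.** Let f be the fraction lost. The full-group mean is (1 − f) × completer mean + f × leaver mean, so

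overstatement = f × (completer mean − leaver mean).

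Assumptions, none of them in the documents: change scaled to SD 1; true 24-week change 0.8; correlation between the Visit 5 and Visit 7 changes of 0.5 to 0.85; baseline correlation 0.3; logistic dropout with slope 1.5 per SD of poorer response.

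- *Leaving depends on the observed Visit 5 change.* At f = 4/30 this slope shifts the completers' mean Visit 5 change by 0.158 SD. The Visit 7 shift is correlation × 0.158: 0.5 gives 0.079, 0.7 gives 0.110 and 0.85 gives 0.134. Simulation with 2,000,000 subjects gave 0.078, 0.111 and 0.133. As a share of 0.8, that is 10% to 17%.
- *Leaving depends on the unseen Visit 7 change.* The shift is about 0.156-0.158 SD, or 20%.
- By the identity above, 0.08 to 0.16 SD means that leavers do worse than completers by 0.08/0.133 = 0.6 to 0.16/0.133 = 1.2 SD.
- *Ceiling, if exactly the worst 13.3% leave.* φ(−1.111)/(1 − 0.133) = 0.2153/0.8667 = 0.248 SD, or 31%.
- At 20% and 30% dropout the overstatement is 14-28% and 20-41%.

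**3. Against sampling error.** With 26 completers the standard error is 1/√26 = 0.196 SD, so 0.08 to 0.16 SD is 0.4 to 0.8 of a standard error. For weight, assume a change of −3 kg with SD 3.75 kg (again 0.8 SD). A separate simulation with a milder slope of 1.2 and correlation 0.7 gave 0.25 kg at 9% dropout and 0.31 kg at 12%. The standard error there is 3.75/√26 = 0.74 kg.

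**4. What a three-visit likelihood model removes, at 4 of 30 lost.**

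| When and why people leave | Completer bias (SD) | Model bias (SD) | Share removed |
|---|---|---|---|
| All after Visit 5, explained by Visit 5 value | 0.08 to 0.13 | 0.00 | about 100% |
| Half before Visit 5, rest explained by Visit 5 value | 0.08 to 0.14 | 0.03 to 0.07 | 54-58% |
| All after Visit 5, driven by unseen Visit 7 response | 0.16 | 0.05 to 0.12 | 24-69% |
| Half before Visit 5, rest driven by unseen response | 0.13 to 0.15 | 0.09 to 0.10 | 21-41% |
| All before Visit 5 | 0.08 to 0.13 | 0.07 to 0.12 | 9-17% |

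In 4,000 simulated trials of n = 30 (correlation 0.7; first, second and fourth rows), the empirical standard error was 0.18 to 0.19 SD for both methods. In no scenario tried was the model more biased than the completer mean.

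**The case against.** Several counter-arguments stand, and they limit the point.

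- A reader might infer that paired t-tests drop everyone who leaves. They do not. Someone lost after Visit 5 still counts in the Visit 2-5 test, which is the main secondary contrast. For that contrast the model adds almost nothing, because anyone lost earlier has only a baseline value.
- A reader might infer that a mixed model avoids most of the bias. That holds only in the first row of the table in the working.
- A reader might take poor-responder dropout as given. Nothing in the article says who will leave or when, so the direction of the bias is conditional.
- The sentence in section 2.9 covers baseline against post-intervention. It does not name a test for Visits 5-7, so a paired test for every Table 2 contrast is not literally stated.
- Missing-data rules are commonly left to a fuller protocol or analysis plan, and their absence from an article is no finding.
- The cardiometabolic outcomes are labelled exploratory. The Discussion asks for caution because there is no control group, and section 2.1 promises retention and reasons for dropout.

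What survives is narrower. The article commits to a two-timepoint test in a three-visit design, and for the Visit 2-7 change that test sets aside observed data whatever the reason for dropout. The Discussion's caution gives monitoring as its example and does not mention selective loss.

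**Conclusion.** The point holds for the 24-week change, as a worthwhile improvement and not as a fatal flaw. If poorer responders leave more often and 4 of 30 are lost, the completer mean overstates a true 0.8 SD change by roughly 10-20%, which is less than one standard error. The direction and size rest on the assumed correlation, dropout slope and timing of loss; only the 30 enrolled, the 26 analysed and the effect size of 0.8 come from the document. The documents do not support a claim that the 24-week result will be biased, that the Visit 2-5 result is affected in the same way, or that a mixed model removes the problem in general.

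**What to change.** For outcomes measured at Visits 2, 5 and 7, replace the paired t-tests with one linear mixed model per outcome. Use visit as a fixed factor, an unstructured within-person covariance and all available values from everyone who started TRE. Report the Visit 2-5, 5-7 and 2-7 contrasts with 95% confidence intervals. For app outcomes, use the baseline period and the Visit 5 and Visit 7 periods as the time factor.

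Keep the paired t-test as a completer sensitivity analysis, and report the numbers lost before and after Visit 5. Because the model cannot correct for leaving driven by an unseen poor response, a sensitivity analysis that sets leavers to zero change, or applies a delta adjustment, would show how far that matters.

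The cost is a change of analysis wording, slightly more analysis work and reliance on a missing-at-random assumption. The planned software can fit the model, and with complete data the contrasts equal the paired differences.

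The change does little for losses before Visit 5 or for the main Visit 2-5 contrast.

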## 3. Results

The TREMNIOS trial is currently recruiting participants. The estimated primary completion date of the study is July 2022. The TRE intervention is expected to improve cardiometabolic markers and daily rhythms of behavior in patients with MetS and prolonged daily eating period.

## 4. Discussion

To our knowledge, the TREMNIOS pilot clinical trial in Poland is the first study targeted at collecting comprehensive data on the feasibility and exploratory data on the effectiveness of TRE for improving cardiometabolic health and daily rhythms of behavior in the European adult population of patients with MetS and prolonged daily eating period. The protocol of TREMNIOS trial extends the previous TRE-related protocols by targeting European population of patients with diagnosed MetS and including longer duration of TRE intervention, validated tools for recording food intake and monitoring an adherence to intervention, as well as more comprehensive range of metabolic, neuroendocrine, oxidative stress and inflammatory biomarkers. The study will lay the essential groundwork for a planned large-scale randomized controlled trial to determine the effectiveness and sustainability of TRE for reducing long-term cardiometabolic risks in patients with MetS.

The rationale for the TREMNIOS trial builds largely on extensive mechanistic molecular and physiological studies of circadian rhythms, eating patterns, and metabolic homeostasis, both in animal models and human studies, as well as the findings of several previous small-scale TRE human trials. Although TRE provides a promising strategy for the prevention and treatment of cardiometabolic diseases, evidence on the effectiveness of TRE in patients with MetS is limited, thus further focused studies are needed. Importantly, there is a paucity of information about the feasibility and long-term sustainability of an implementation of TRE as an alternative approach in the management of the European populations of patients with MetS, and there is limited data on effects of TRE on cardiometabolic outcomes in these populations.

Several small-scale TRE studies in healthy humans with normal weight demonstrated that TRE can be feasible, safe, and beneficial dietary strategy [48,49,50,51,52,53,54,55]. TRE resulted in a decrease in energy intake [48,51], body weight even without reducing calorie intake [48,49], body fat even without impacting lean mass [49,50,52,54], BP [49], blood glucose and TG [50], glucose intolerance [55], leptin and inflammatory markers levels [50], and feeling of hunger [55], as well as an increase in adiponectin and HDL-cholesterol levels [49,50], muscular strength, and endurance capacity [51,52,55]. Although no significant impact of TRE on body weight [50,51], body fat [51], glucose and insulin levels [49,52], some lipids [49,50,52], inflammatory markers [55], and cortisol pattern [49,52] or even worsening of glucose metabolism measures [53] were observed in several studies of healthy subjects, available data indicated that TRE can be effective for improving cardiometabolic outcomes.

To our knowledge, one pilot study of an American population of patients with diagnosed MetS [34] and several small-scale TRE trials in the populations (mainly from the US) with elevated BMI (overweight or obese subjects) [25,35,36,37,38,40,41,42,44,45,46], increased waist circumference (individuals with central obesity) [39,40,43], and disorders of glucose metabolism (subjects with prediabetes, high risk of T2DM, and T2D with controlled hyperglycemia (HbA1c < 9%) either by diet or taking ≤ two oral hypoglycemic agents) [37,39,47] were conducted. The trials of individuals with metabolic disorders demonstrated that TRE result in several cardiometabolic benefits such as weight loss [25,34,35,38,39,40,43,44] and a decrease in body fat [34,35,36,43,44] and energy intake [25,34,36,38,44,47], as well as improved glucose tolerance [39], insulin resistance [37,38,41,44], glycemic control [35,36,39,41,43,45], lipid levels [34,39], sleep [25], quality of life [25,40,45], and reduced BP [34,37,38]. In the pilot study of American patients with MetS, the improvements in body weight and fat, waist circumference, atherogenic lipids, and BP were observed despite no overt attempt to change diet quantity and quality or physical activity [34]. Moreover, previous TRE trials of subjects with metabolic disorders reported good adherence with TRE for a period up to 16 weeks [25,34,35,38,43,47].

Despite the encouraging results of previous TRE human studies, various aspects associated with an implementation of TRE in patients with diagnosed MetS require further clinical research which should be conducted exclusively in such populations of patients. Specifically, long-term feasibility of TRE intervention deserves further attention. In the pilot study of American population with MetS, the adherence to TRE and mCC app during a 12-week period was shown to be ~90 and ~85%, respectively [34]. In the study of diabetic patients, the rate of adherence varied greatly from 4% to 100% even over a relatively short period of 4-week TRE intervention [47]. This indicates that the adherence to TRE can be variable and is not always satisfactory. Wilkinson et al. [34] also observed that self-selecting of TRE eating window may be conducive to better adherence to TRE intervention. However, data on the extent to which MetS patients maintain a shortened daily eating window for an extended period of time during TRE intervention is lacking. The TREMNIOS trial is expected to provide insights into this question by evaluating the adherence of MetS patients to TRE over a relatively long period of 24 weeks. The TREMNIOS data characterizing the feasibility will aid in the design of a larger randomized controlled trial.

The impact of TRE on weight loss, decrease in body fat, energy restriction, decreasing appetite, and delimitation of eating window as well as the interactions between these TRE effects require elucidation. In addition, the effects of TRE on glycemic measures and lipid levels require further investigation as available data are limited and highly variable. Specifically, in several studies, no significant TRE-related improvements of some glucose or lipid measures were observed [34,35,36,37,38,39,40,43,45,46,47]. In addition, some findings suggest an increase in lipids post-early TRE or elevated FPG and morning glucose intolerance post-late TRE [37,41,53]. Moreover, TRE effects on metabolic, inflammatory, and oxidative stress biomarkers have been poorly investigated, so further evidence is needed regarding potential post-TRE improvements in oxidative stress, inflammation, and atherosclerosis [37,41,44,50,60]. In addition, more data on potential benefits of TRE on circadian-related metabolic and neuroendocrine biomarkers, BP, and daily rhythms of behavior such as eating window, meal timing, sleep, and physical activity would be desirable [63,64,65].

In addition to targeting an European population of patients with MetS, the protocol of TREMNIOS trial extends the protocols used in recent and ongoing TRE-related studies [25,34,35,38] by including exclusively patients with diagnosed MetS, longer duration of TRE intervention (of 24 weeks), more comprehensive range of various cardiometabolic biomarkers including circadian-related hormones, analyses of biomarkers at multiple time points over a period of 6 months, application of CGM for an evaluation of glucose control, use of mCC app as the validated method for recording eating pattern and nutrient intake, sleep, activity and monitoring of an adherence to TRE, as well as additional tools for chrono-nutrition assessment. These extensions are important to advance an understanding of the roles of metabolic regulatory mechanisms and circadian system in the pathophysiology of MetS and its complications. Available data seem to support a 10 h TRE eating window that has been chosen for this trial. This window still produces benefit and long-term adherence is expected to be better compared to the application of more restrictive eating period [25,34]. The multi-approach methodology will provide a means to comprehensively evaluate the feasibility of TRE and provide an exploratory data on the impact of TRE on eating pattern, nutrient intake, metabolic homeostasis, and overall health of the population of patients with MetS during the 6-month TRE intervention.

The TREMNIOS trial is expected to lay the essential groundwork for a planned large-scale randomized controlled trial to determine if adopting a simple TRE pattern intervention can lead to restoring rhythmic daily behavior resulting in a reduction of cardiometabolic risks and improvements of health status in Polish population of patients with MetS and prolonged daily eating period. The results of this trial will be useful for a design of future large-scale trial in terms of sample size, inclusion/exclusion criteria, duration and timing of TRE eating window, length of TRE intervention, primary and secondary outcomes, use of the mCC app, and spectrum of biomarkers for evaluating the efficacy of TRE intervention in patients with MetS. TRE studies on the American populations of patients with MetS have been recently undertaken in the US under the leadership of scientists who are the members of TREMNIOS research team ([name], [name], and [name]). The initiation of acquisition of TRE-related data for the European population of patients through the TREMNIOS trial and the use of consistent protocols will facilitate creation of joint databases and comparative analysis of patient populations with MetS from different countries and continents.

The TREMNIOS trial will examine one group of 30 patients (pre-post TRE intervention) with no control group which is a potential limitation. This approach has been chosen given that this trial is a precursor for large-scale controlled trial in the future and available funding at this initial stage of study is limited which limits the overall number of patients. Following the results of power analysis, it is deemed advantageous to conduct a single arm trial with 30 participants rather than the controlled trial with a smaller sample size of each group. Whereas the evaluation of the adherence to the TRE intervention does not require a control group, the interpretation of exploratory data on cardiometabolic parameters will require caution. For example, because there is no control group, one cannot exclude the possibility that TRE-related changes in cardiometabolic parameters will be to some extent affected by the process of monitoring during the TRE intervention. The planned randomized controlled trial to be conducted after the TREMNIOS trial is expected to be free of this limitation. However, the lack of a control group in the TREMNIOS trial may limit the ability to predict the acceptability of participants to be randomized to intervention and control groups in a planned large-scale randomized-control trial.

